## Abstract

**Rationale/Aim:**

Intracranial atherosclerotic stenosis (ICAS) is a common cause of stroke in Asia and is significantly associated with stroke recurrence. The Balloon angiopLasty for intracranial Atherosclerotic minor Stroke/TIA (BLAST) study aims to evaluate the safety and effectiveness of early submaximal balloon angioplasty (SBA) combined with standard medical therapy vs. standard medical therapy alone in patients with minor stroke or transient ischemic attack (TIA) due to ICAS.

**Methods:**

The BLAST study is a multicenter prospective cohort study which will enroll patients with minor stroke or TIA due to symptomatic ICAS within 1 week of symptom onset from 20 centers in China. Eligible patients will receive either SBA with standard medical therapy or standard medical therapy alone based on the decision of the patient or legal representative. Participants will be followed up for 1 year.

**Study outcomes:**

The primary outcome is a composite of stroke or death within 30 days or ischemic stroke in the culprit artery territory from 30 days to 1 year. Secondary outcomes include stroke or death within 30 days, ischemic stroke in the culprit artery territory from 30 days to 1 year, restenosis rate of the culprit artery at 1 year, and neurological improvement at 90 days (assessed by mRS score). Safety outcomes include intracranial hemorrhage within 30 days and endovascular complications.

**Sample size estimate:**

According to previous studies, the incidence of the composite clinical outcomes is 15% in the group receiving medical therapy alone. We assumed the incidence would decrease to 5% in the SBA combined with the medical therapy group. The target sample size is 416 patients (208 per group), with 90% power and 5% type I error, allowing for a 10% loss to follow-up.

**Implications:**

The BLAST study will provide evidence regarding whether early SBA can reduce stroke recurrence and mortality in patients with minor stroke/TIA due to ICAS compared with medical therapy alone.

**Clinical trial registration:**Clinicaltrials.gov, NCT06014723.

## Introduction

In China, stroke is the leading cause of death, and its burden is substantial (1). Intracranial atherosclerotic stenosis (ICAS) is a common cause of stroke and transient ischemic attack (TIA) worldwide, particularly in Asia (2–5). The recurrence rate of stroke caused by ICAS within 1 year was found to be as high as 20% (6–8). Therefore, preventing recurrence after a stroke with ICAS is an important area for study.

Over the past 20 years, several trials have investigated stent placement combined with medical therapy in this population; however, the results have been neutral, and the risk of recurrent stroke remains high (9–11). Compared with stenting, submaximal balloon angioplasty (SBA) could be a safer and simpler intervention that may be an effective strategy for preventing recurrent stroke (12, 13). For example, prior meta-analysis found that the incidence of stroke or death within 30 days after SBA was 3–4.9% (14, 15), and the one-year stroke occurrence rate was 5% (15), which was lower than that of stent placement (9–11).

Minor stroke, defined as a National Institutes of Health Stroke Scale (NIHSS) score ≤ 5, accounted for about half of acute ischemic stroke patients (16, 17). There is high risk of early recurrence of stroke in this population, especially caused by ICAS although enhanced medical treatment was administrated (18, 19). To date, no systematic investigation has compared the effectiveness of SBA combined with standard medical therapy vs. standard medical therapy alone in patients with minor stroke/TIA with ICAS. Therefore, we design a multicenter prospective cohort study to evaluate the safety and effectiveness of early SBA combined with medical therapy vs. medical therapy alone in minor stroke/TIA patients with ICAS.

## Methods

### Study design

The Balloon angiopLasty for intracranial Atherosclerotic minor Stroke/TIA (BLAST) study is a multicenter prospective cohort study designed to investigate the safety and effectiveness of early SBA combined with medical therapy vs. medical therapy alone in patients with minor stroke/TIA with ICAS. This study was approved by the Ethics Committee of the First Hospital of Jilin University (NO.23K081) and other participating hospitals. The study was registered at ClinicalTrials.gov (NCT06014723).

### Target population

A total of 416 patients from 20 hospitals in China will be enrolled and allocated to either the SBA group (*n* = 208) or the control group (*n* = 208) based on patient treatment preferences. These centers are chosen based on high-capacity centers with neurointervention and good cooperation experience. Eligible patients are adults aged 30–80 years with symptomatic ICAS (70–99% stenosis) resulting in minor stroke (NIHSS score ≤ 5) within 1 week of onset or from symptom exacerbation (NIHSS score increased by ≥2 points) or intermediate- to high-risk TIA, defined as ABCD2 score ≥ 4 within 1 week of the last symptom episode based on radiologic and clinical presentation. Eligible lesions include the intracranial segment of the internal carotid artery (segments C4–C7), the M1 segment of the middle cerebral artery, the V4 segment of the vertebral artery, and the basilar artery. The main exclusion criteria include allergy to contrast media non-atherosclerotic disease-related stenosis; penetrating branch lesion ipsilateral to the target lesion; presence of severe stenosis of the extracranial segment on the side of the target lesion; previous endovascular treatment of the ipsilateral vessel; presence of intracranial aneurysms, tumors, and vascular malformations; any form of ipsilateral intracranial hemorrhage within 3 months and contralateral intracranial hemorrhage within 2 weeks; presence of atrial fibrillation, severe heart dysfunction, liver or kidney dysfunction; patients with tumors and serious diseases whose expected survival time is ≤1 year; and others. The detailed inclusion/exclusion criteria are listed in Table 1. Before enrolling the first patient, all participating centers will receive standard training on the study protocol, inclusion/exclusion criteria, and other relevant details. Patients who meet the inclusion criteria and those who do not meet the exclusion criteria will be eligible to participate (Figure 1). All patients and their legal representatives will be required to sign informed consent.

**Table 1 tab1:** Inclusion and exclusion criteria.

**Inclusion criteria**
1.age range of 30–80 years;
2.symptomatic ICAS (C4–C7 segments of ICA, M1 segment of the MCA, V4 segment of the VA, and BA) with 70–99% stenosis confirmed by DSA;
3.minor stroke (NIHSS score ≤ 5) within 1 week of onset or from symptom exacerbation (NIHSS score increased by ≥2 points) or intermediate- to high-risk TIA, defined as ABCD^2^ score ≥ 4 within 1 week of the last symptom episode;
4.diameter of the culprit artery ranging from 2.0 to 4.5 mm, and the length of the stenosis≤14 mm;
5.mRS ≤ 2 before endovascular treatment;
6.no large ischemic region found on CT or MRI (ASPECTS ≥ 6 or pc-ASPECTS ≥ 8);
7.written informed consent obtained from the patient or legally responsible person.

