### Treatment strategy

#### The SBA group

In the SBA group, patients will undergo SBA within 1 week of stroke or TIA onset on the basis of standard medical therapy (20). SBA aims to improve stenosis of the culprit artery by more than 20%.

The procedure involves the following steps: (1) Under general or local anesthesia, femoral artery access is obtained, and heparinization is performed (trans-radial access may be used for posterior circulation, aortic arch or abdominal aortic tortuosity); (2) A 6–8F guide catheter is selected per operator preference (an access catheter may be used if the anatomy is tortuous); (3) The diameter of the stenosis, diameter of the artery proximal and distal to the artery is measured; (4) An 0.014 microwire is passed through the lesion into the distal branch of the artery, with microcatheter assistance as needed; (5) The balloon with a diameter of 50–80% of the normal vascular diameter is advanced over the microwire to the lesion, and is slowly inflated (1 atm/min) for 30–120 s, then deflated. If no major dissection or rupture is observed, the balloon is withdrawn while the wire remains in place. Intraprocedural antiplatelet therapy (glycoprotein IIb/IIIa receptor antagonist) may be administered as needed; (6) Angiography is performed after balloon removal to assess the stenosis. If the stenosis is improved by >20% without major dissection, repeat angiography is done within 10–15 min. If the improvement is maintained, the procedure is complete; otherwise, up to 3 repeat dilatations may be performed.

Rescue stenting may be performed if the following occurs: (1) After SBA, residual stenosis remains>80% or forward flow is unstable with a modified Thrombolysis in Cerebral Infarction (mTICI) score < 2b; (2) local dissection causes unstable distal flow and mTICI < 2b.

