#### The control group

In the control group, patients will receive standard medical therapy based on current guidelines (20). The antithrombotic regimen will be aspirin 100 mg daily for the duration of follow-up and clopidogrel 75 mg daily for 90 days after enrollment, with continuation determined by the local investigator. For clopidogrel-resistant patients, the investigator may switch to ticagrelor. Lipid-lowering therapy with statins or PCSK9 inhibitors will achieve a low-density lipoprotein target of <1.8 mmol/L (70 mg/dL). Blood pressure will be maintained at <140/90 mmHg.

Timely and positive control of risk factors in both groups will include smoking cessation, a low-salt, low-fat diet, and appropriate exercise.

In the prospective cohort study, eligible patients will receive either SBA with standard medical therapy or standard medical therapy alone based on the decision of the patient or legal representative.

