### Outcomes

The primary outcome is a composite of stroke (hemorrhagic and ischemic), or death within 30 days, or ischemic stroke in the culprit artery territory from 30 days to 1 year. Secondary outcomes will include stroke (hemorrhagic and ischemic) or death within 30 days, ischemic stroke in the culprit artery territory from 30 days to 1 year, restenosis of the culprit artery at 1 year defined as exceeding 50% of the stenosis degree or narrowing reaching or surpassing the stenosis degree at the time of the procedure, and neurological functional outcome at 90 days (assessed using the mRS score). Safety outcomes include intracranial hemorrhage within 30 days and endovascular complications. Follow-up will occur at 24 h, discharge, 30 days, 90 days, and 1 year after enrollment. All clinical outcomes including stroke and mRS will be evaluated by certified assessors who are blinded to allocation treatment.

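### Inclusion criterion 5 times the mRS check to a procedure that only the SBA group has, so it has no assessment time for controls and could permit post-enrolment selection in the SBA group

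*Protocol article*

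**What the plan says.** Table 1 of the Protocol article has one inclusion list. Its fifth item requires an mRS of 2 or less "before endovascular treatment". No item is marked as applying to one group only, and the Target population section treats the list as common: "Patients who meet the inclusion criteria and those who do not meet the exclusion criteria will be eligible to participate".

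The other relevant statements are these:

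- **Allocation** is by preference. Patients receive SBA plus medical therapy or "standard medical therapy alone based on the decision of the patient or legal representative" (The control group).
- **Timing of SBA**: "patients will undergo SBA within 1 week of stroke or TIA onset" (The SBA group). The interval from enrolment to the procedure is not given.
- **Follow-up** visits include "30 days, 90 days, and 1 year after enrollment" (Outcomes), with no distinction between groups.
- **Primary outcome** (Outcomes): any stroke or death within 30 days counts, as does later ischemic stroke in the culprit territory up to 1 year.
- **Adjustment** (Data analysis): age, sex, baseline NIHSS, pre-stroke mRS, and TIA versus stroke.

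**The concern.** An eligibility criterion should be assessable at the same point for everyone being compared. This one refers to an event that only one of the two groups is planned to have. For the 208 planned control patients, the text does not say when mRS is to be judged.

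The gap matters because of the setting. The Introduction describes a high early risk of recurrence in this population, and a stroke in the first 30 days is a primary event. If a centre takes the wording at face value and judges mRS shortly before the procedure, an SBA chooser who has a disabling stroke while waiting no longer meets the criterion and may be left out. A control patient with the same stroke on the same day was already eligible and contributes an event. Early events would then be lost from one group only, in the direction that favours SBA. Adjustment for baseline covariates cannot bring back events that were never counted.

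**Working it through.** **Step 1: the passages side by side.** Criterion 5 is common to all participants (Table 1, Target population). Its time anchor is endovascular treatment. The control group has no planned endovascular treatment (The control group section). So the criterion is defined for SBA patients and undefined in time for controls. This step needs no assumption.

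**Step 2: when this becomes a bias.** Three conditions must all hold: (a) some time passes between enrolment and SBA; (b) mRS is judged late in that time, after enrolment; (c) patients then above mRS 2 are left out of the SBA group. The article neither states nor rules out any of them.

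**Step 3: the plan's own figure.** Sample size estimates gives 15% versus 5%, two-sided alpha 0.05 and 90% power. The unpooled normal formula gives n per group = (0.15×0.85 + 0.05×0.95) × (1.960 + 1.282)² / 0.10² = 183.9, rounded up to 184, or 368 in total. This matches the article. The total of 416 less 10% loss leaves about 374, or 187 per group. The concern does not affect these figures.

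**Step 4: illustration of size.** The assumptions, none of which the documents give, are:

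- no true effect, with 15% events in both groups;
- 187 evaluable patients per group;
- a share w of SBA choosers who have a primary event leaving them above mRS 2 before the procedure, all of whom are left out.

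These patients leave both the numerator and the denominator, so the observed SBA rate is p = (0.15 − w)/(1 − w). The chance of a significant result favouring SBA is approximately Φ(z − 1.96), with z = (0.15 − p)/√[(0.15×0.85 + p(1 − p))/187].

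| w (assumed) | p | Apparent difference | z | Chance of a false finding for SBA |
|---|---|---|---|---|
| 0 | 15.0% | 0 | 0 | 2.5% |
| 1% | 14.1% | 0.9 points | 0.24 | 4.2% |
| 2% | 13.3% | 1.7 points | 0.48 | 7.0% |
| 3% | 12.4% | 2.6 points | 0.74 | 11.1% |

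This is an unadjusted comparison of two proportions. The plan uses adjusted regression, so the table shows direction and order of magnitude, not a forecast. With mRS fixed at enrolment in both groups, w = 0 and this bias is absent.

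**The case against.** The strongest reply is that an inclusion criterion is naturally read as one check at eligibility, before any treatment, for everybody. The list is common to both groups, and nothing is waived for controls. The article has no rule for repeating mRS after enrolment or for withdrawing patients who worsen. Allocation by preference and follow-up from enrolment already point towards grouping by decision, so that an SBA chooser's stroke while waiting would count against SBA. The enrolment-to-procedure interval may be short: SBA falls within a week of onset, and enrolment already requires stenosis confirmed by DSA. The flowchart that might settle the order of steps is not visible here. The analysis set may be defined in a fuller document.

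Much of this stands. A reader might infer that criterion 5 screens the SBA group alone, or that it removes patients who worsen and so builds in an immortal-time bias. The documents do not support either: the list is common, and no removal is described. Nor would all early recurrences be lost even on the literal reading, only those that leave mRS above 2 before the procedure. A 3% loss would mean that one fifth of the planned 15% one-year event rate fell in this interval and was dropped. And the absence of an analysis-set definition from an article is not itself a fault.

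What the reply does not remove is the stated anchor. Data analysis uses the separate term pre-stroke mRS, so the benign reading of criterion 5 is possible but not what it says. Twenty centres could apply it differently, and without randomisation nothing in the design evens out such differences.

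**Conclusion.** The point holds in a limited form. Criterion 5 applies to all participants but has no defined assessment time for controls. On a literal reading it could allow selection on a post-enrolment state in the SBA group only, which would favour SBA and would not be corrected by the planned covariates.

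Whether that happens depends on the three conditions in Step 2, and the documents do not give its size. Under the assumptions of Step 4, a loss of 1 to 3% would raise the one-directional error from 2.5% to about 4 to 11%. Those losses are assumed, not estimated. The point merits a change because the correction is small and reduces a possible bias in a design that has no randomisation. It does not show that the study is biased.

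**What to change.** 1. In Table 1, time the mRS assessment in criterion 5 to enrolment for both groups and leave the threshold as it is.
2. State that the group is set by the treatment decision recorded at enrolment.
3. State that all events are counted from enrolment in that group, including those of SBA choosers who worsen before the procedure or never have it.

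**Cost:** one table line and one or two sentences of analysis text. The downside is slight dilution of the estimated effect by SBA choosers who do not receive SBA. The article reports 40 of 416 patients recruited at first submission, with recruitment planned to December 2026, so early clarification would cover most of the cohort. For patients already enrolled, it would help to record when mRS was assessed and whether any SBA chooser was left out before the procedure.

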**Exclusion criteria**
1.allergy to contrast media;
2.non-atherosclerotic disease-related stenosis, such as arterial dissection, Moya-Moya disease, and arteritis;
3.penetrating branch lesion ipsilateral to the target lesion (infarction caused by penetrating branch occlusion is defined as stenosis of the MCA or BA, but only with simple basal ganglia or brainstem/thalamic infarction);
4.presence of severe stenosis of the extracranial segment on the side of the target lesion;
5.previous endovascular treatment of the ipsilateral vessel;
6.presence of intracranial aneurysms, tumors, and vascular malformations;
7.any form of ipsilateral intracranial hemorrhage within 3 months and contralateral intracranial hemorrhage within 2 weeks;
8.resence of atrial fibrillation, severe heart dysfunction, liver or kidney dysfunction; patients with tumors and serious diseases whose expected survival time is ≤1 year;
9.hemoglobin ≤100 g/L, platelet count ≤100 × 10^9^/L, INR > 1.5 (irreversible), coagulopathy or irremediable bleeding factors;
10.uncontrollable hypertension: systolic blood pressure > 185 mmHg and/or diastolic blood pressure > 110 mmHg;
11.poor glycemic control (random blood glucose >22.2 mmol/L);
12.history of major surgery within 30 days prior to enrollment or surgery plan within 90 days after enrollment;
13.pregnancy or lactation;
14.other conditions that the researchers think make the patient unsuitable for the study.

ICAS, intracranial atherosclerotic stenosis; ICA, internal carotid artery; MCA, middle cerebral artery; VA, vertebral artery; BA, basilar artery; ASPECTS, Alberta Stroke Program Early CT Score; pc-ASPECTS, posterior circulation ASPECTS; DSA, digital subtraction angiography; NIHSS, National Institutes of Health Stroke Scale; TIA, transient ischemic attack; mRS, modified Rankin Scale; CT, computed tomography; MRI, magnetic resonance imaging; INR, international standardized ratio.

**Figure 1 fig1:**
[figure not shown]
Patient enrollment flowchart. SAE, severe adverse events; DSA, digital subtraction angiography; CTA, computed tomography angiography; MRA, magnetic resonance angiography.

### Treatment strategy

#### The SBA group

In the SBA group, patients will undergo SBA within 1 week of stroke or TIA onset on the basis of standard medical therapy (20). SBA aims to improve stenosis of the culprit artery by more than 20%.

The procedure involves the following steps: (1) Under general or local anesthesia, femoral artery access is obtained, and heparinization is performed (trans-radial access may be used for posterior circulation, aortic arch or abdominal aortic tortuosity); (2) A 6–8F guide catheter is selected per operator preference (an access catheter may be used if the anatomy is tortuous); (3) The diameter of the stenosis, diameter of the artery proximal and distal to the artery is measured; (4) An 0.014 microwire is passed through the lesion into the distal branch of the artery, with microcatheter assistance as needed; (5) The balloon with a diameter of 50–80% of the normal vascular diameter is advanced over the microwire to the lesion, and is slowly inflated (1 atm/min) for 30–120 s, then deflated. If no major dissection or rupture is observed, the balloon is withdrawn while the wire remains in place. Intraprocedural antiplatelet therapy (glycoprotein IIb/IIIa receptor antagonist) may be administered as needed; (6) Angiography is performed after balloon removal to assess the stenosis. If the stenosis is improved by >20% without major dissection, repeat angiography is done within 10–15 min. If the improvement is maintained, the procedure is complete; otherwise, up to 3 repeat dilatations may be performed.

Rescue stenting may be performed if the following occurs: (1) After SBA, residual stenosis remains>80% or forward flow is unstable with a modified Thrombolysis in Cerebral Infarction (mTICI) score < 2b; (2) local dissection causes unstable distal flow and mTICI < 2b.

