### Data analysis

The baseline patient characteristics will be presented in both groups. Categorical variables will be expressed as frequencies and percentages. Chi-square tests will be used to compare differences between groups. Continuous variables will be presented as mean ± standard deviation or median and quartiles after testing for normality using the Kolmogorov–Smirnov test. The Student’s *t*-test or the Mann–Whitney U test will compare group differences based on normality. Missing data will be handled using multiple imputations.

Primary and secondary outcomes will be analyzed using linear or Cox regression, as appropriate, after adjusting for key prognostic factors (age, sex, baseline NIHSS score, and pre-stroke mRS score, and presention with TIA vs. stroke). Statistical analysis will be performed using SPSS 24.0, with two-sided *p* < 0.05 considered statistically significant.

The primary endpoint will further be stratified by age (≤65 vs. >65 years), gender (male vs. female), hypertension (yes vs. no), diabetes mellitus (yes vs. no), smoking (yes vs. no), baseline SBP (<140 vs. ≥140 mmHg), clinical presentation (TIA vs. stroke), mechanism of stroke (i.e., borderzone vs. perforator vs. embolic), lesion location (anterior circulation vs. posterior circulation), whether the patient is already on pre-stroke aspirin or DAPT.

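### Entry counts one week from onset, exacerbation or last TIA, but SBA is timed from onset alone; read literally, some eligible patients could enter only as controls

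*Protocol article*

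**What the plan says.** **Entry.** Inclusion criterion 3 in Table 1, repeated under Target population, accepts minor stroke "within 1 week of onset or from symptom exacerbation", where exacerbation means an NIHSS rise of at least 2 points. It accepts TIA with an ABCD2 score of at least 4 "within 1 week of the last symptom episode".

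**SBA timing.** The section on the SBA group states that "patients will undergo SBA within 1 week of stroke or TIA onset". It mentions neither exacerbation nor the last episode.

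**Control timing.** The section on the control group says "In the control group, patients will receive standard medical therapy based on current guidelines" and sets no time limit beyond eligibility.

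**Choice of group.** The same section says "eligible patients will receive either SBA with standard medical therapy or standard medical therapy alone based on the decision of the patient or legal representative".

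**Summaries of entry.** The abstract describes enrolment "within 1 week of symptom onset from 20 centers in China". The opening of the Discussion also reduces entry to one week after onset.

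**Adjustment.** The Data analysis section lists "age, sex, baseline NIHSS score, and pre-stroke mRS score, and presention with TIA vs. stroke". None of these is a time variable, and none records exacerbation or repeated episodes.

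**The concern.** Criterion 3 joins onset and exacerbation with an "or", so in that criterion onset does not include exacerbation. The SBA section then keeps only onset. If both rules are applied as written, some patients qualify for the study at a time when the SBA window has already closed, while the control group remains open to them.

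This matters more here than in a randomised trial. The comparison rests on patients in one group having counterparts in the other after adjustment. In a stratum where nobody can receive SBA there are no counterparts, and a regression model can only extrapolate. The Discussion itself argues that the benefit of endovascular treatment falls as time from onset grows, so timing is not a neutral variable in this study.

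**Working it through.** **1. The windows side by side**

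| Patient | Eligible until (criterion 3) | SBA window closes (SBA group section) | Days eligible but outside the SBA window |
|---|---|---|---|
| Stroke onset day 0, no exacerbation | day 7 | day 7 | none |
| Stroke onset day 0, exacerbation day 5 | 5 + 7 = day 12 | day 7 | days 8 to 12 |
| First TIA day 0, last TIA day 6; TIA onset read as first episode | 6 + 7 = day 13 | day 7 | days 8 to 13 |
| Same patient; TIA onset read as last episode | day 13 | day 13 | none |

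The second row needs only the words of the two sections. The TIA rows show that the conflict there depends on what TIA onset means.

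**2. How large the effect could be**

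The article gives neither the share of such patients nor their risk, so the following values are assumptions:
- *f*: share of controls who come from the control-only stratum (assumed).
- *r*: their risk relative to the other patients (assumed).
- Base risk *p* = 15%, the medical-therapy rate in the Sample size section.
- SBA has no effect.
- Evaluable patients per group: 416 × 0.90 / 2 = 187.2, taken as 187.

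Formulas:
- Control risk: *p*c = *p* × [1 + (*r* − 1)*f*].
- Spurious risk ratio, SBA to control: 1 / [1 + (*r* − 1)*f*].
- Spurious difference: *d* = *p*c − *p*.
- Probability of a two-sided p < 0.05: Φ[(*d* − 1.96·s0)/s1] + Φ[(−*d* − 1.96·s0)/s1]. Here s0 = √[2·p̄(1 − p̄)/187], with p̄ the mean of the two risks, and s1 = √{[*p*c(1 − *p*c) + *p*(1 − *p*)]/187}.

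| *f* | *r* | Control risk | Spurious RR | Difference (points) | False-positive rate |
|---|---|---|---|---|---|
| 5% | 1.5 | 15.4% | 1/1.025 = 0.98 | 0.4 | 5.1% |
| 10% | 1.5 | 15.75% | 1/1.05 = 0.95 | 0.75 | 5.5% |
| 10% | 2 | 16.5% | 1/1.10 = 0.91 | 1.5 | 6.8% |
| 20% | 2 | 18.0% | 1/1.20 = 0.83 | 3.0 | 12.2% |
| 20% | 0.5 | 13.5% | 1/0.90 = 1.11 | −1.5 | 7.0% |

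These figures are unadjusted. In the last row the bias runs against SBA.

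**3. Sample size**

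The point does not touch it. The unpooled normal formula for 15% against 5%, with 90% power and two-sided 0.05, gives 184 per group, or 368 in total, as the article states.

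**The case against.** The best defence is that onset is shorthand. The abstract and the Discussion use it loosely for the whole cohort that Table 1 defines in full, and the SBA section may do the same for the qualifying event. The promise of a choice to every eligible patient supports that reading, because a control-only stratum would contradict it. This may well be what the sponsor intends. But the article does not say so, criterion 3 treats onset and exacerbation as different things, and 20 centres could apply the sentence differently.

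The TIA branch is open to a stronger reply: a TIA is a discrete episode, and its onset readily means that of the last one. That reply stands, and the point rests mainly on the exacerbation branch.

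A reader might go further than the text allows in three ways:
- **That these patients can never receive SBA.** This is an inference from the literal wording. No passage sends them to the control group, and a site could treat them as a deviation from the SBA section.
- **That unstable patients gather in the control group and flatter SBA.** Higher risk after exacerbation is plausible but not documented, and the sign reverses if the risk is lower. Adjustment for baseline NIHSS and for TIA versus stroke may also absorb part of any difference.
- **That controls can enrol at the very end of day 7 while SBA patients cannot.** This is minor. Angiographic confirmation is required of everyone, and no delay from enrolment to SBA is documented.

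**Conclusion.** The stated rules conflict and should be reconciled. The conflict is firm for stroke with later exacerbation and uncertain for TIA. Taken literally, it creates a stratum without overlap in a preference-allocated comparison, and the listed covariates do not capture timing.

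Whether that stratum has any members, how large it is and which way it would push the result cannot be learned from the article. Over the assumed range the effect runs from negligible to a spurious risk ratio of about 0.83, and to about 1.11 in the other direction. This is an inexpensive inconsistency to remove, not a demonstrated bias.

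**What to change.** 1. Reconcile the abstract, Target population, criterion 3, the SBA group section and the opening of the Discussion, so that one reference event and one window govern both entry and SBA timing in both groups. Which event and window is for the investigators to decide.
2. Add time from the qualifying event to enrolment to the adjustment model in the Data analysis section.
3. Run a sensitivity analysis that leaves out, in both groups, patients who at their enrolment were outside the SBA window then in force. Tying this to the window in force matters: if the SBA window is later widened, a rule based on the new window would leave out nobody.

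Step 2 does not replace step 3. The patient with exacerbation on day 5 who enrols on days 8 to 12 is 3 to 7 days from the qualifying event, so the covariate alone would not single that patient out.

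**Cost.** A wording amendment, one more covariate, and possibly a few early patients left out of the sensitivity analysis. If the investigators settle on onset as the only clock, the eligible population also narrows, which is more than a change of wording. At first submission 40 of 416 patients (9.6%) had been recruited, so an early correction would affect few of them.
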